## Abstract

**Background:**

Prophylactic central neck dissection in clinically low-risk cT1bT2N0 papillary thyroid carcinoma is controversial, due to a large number of conflicting retrospective studies, some showing an advantage in terms of locoregional recurrence, others showing no advantage. These previous studies all show high rates of excellent response. We aim to demonstrate the non-inferiority of thyroidectomy alone as compared to total thyroidectomy with prophylactic central neck dissection in conjunction with adjuvant RAI 30 mCi with rTSH stimulation in terms of excellent response at 1 year.

**Trial design and methods:**

Prospective randomized open multicenter phase III trial including patients with 11–40-mm papillary thyroid carcinoma (Bethesda VI) or suspicious cytology (Bethesda V) confirmed malignant on intra-operative frozen section analysis, with no suspicious lymph nodes on a specialized preoperative ultrasound examination. Patients will be randomized 1:1 into two groups: the reference group total thyroidectomy with bilateral prophylactic central neck dissection, and the comparator group total thyroidectomy alone. All patients will receive an ablative dose of 30mCi of radioactive iodine (RAI) within 4 months of surgery. The primary outcome is to compare the rate of excellent response at 1 year after surgery between the groups, as defined by an unstimulated serum thyroglobulin (Tg) level ≤ 0.2 ng/mL with no anti-Tg antibodies, an normal neck ultrasound and no ectopic uptake on the post-RAI scintiscan. Non-inferiority will be demonstrated if the rate of patients with excellent response at 1 year after randomization does not differ by more than 5%. Setting the significance level at 0.025 (one-sided) and a power of 80% requires a sample size of 598 patients (299 per group). Secondary outcomes are to compare Tg levels at 8 +/− 2 postoperative weeks, before RAI ablation, the rate of excellent response at 3 and 5 years, the rate of other responses at 1, 3, and 5 years (biochemical incomplete, indeterminate, and structurally incomplete responses), complications, quality of life, and cost-utility.

**Discussion (potential implications):**

If non-inferiority is demonstrated with this high-level evidence, prophylactic neck dissection will have been shown to not be necessary in clinically low-risk papillary thyroid carcinoma.

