Our study differs from these published studies in the following ways:Our study includes only tumors ≥11 mm (microcarcinomas are not eligible), whereas all of the studies cited in Table 1, with the exception of the study by Sippel et al. [32], included a large proportion of microcarcinomas (in Ahn et al. [31] for example, 90% of the tumors were T1 with a mean tumor size of 1.1 +/− 0.6 cm);Thyroglobulin measurements will be evaluated before and after the administration of RAI to evaluate the effect of RAI ablation and eliminate this bias found in most of these studies in which outcomes were evaluated after RAI ablation in most or all patients;Finally, our study is designed with a non-inferiority margin of 5% and an alpha level set at 0.025, whereas the study by Viola et al. [34] is significant but with a non-inferiority margin of 15% and an alpha of 0.05.

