### Rationale: choice of comparators

In France, total thyroidectomy with prophylactic central compartment (level VI) neck dissection as defined by the American Thyroid Association [38] is standard treatment recommended by the French Society of Otolaryngology Head and Neck Surgery,[15] whereas total thyroidectomy alone without neck dissection is recommended as standard treatment by the Francophone Association of Endocrine Surgery [19].

A simulation by the American Thyroid Association, hypothesizing a 25% difference in significant oncologic events at 7 years, with a statistical power of 80%, concluded that a randomized trial was “not readily feasible” due to the need to randomize 5840 patients [39]. This implies that both therapeutic strategies may indeed be equivalent within a small percentage, and we have therefore designed our study with a *non-inferiority statistical design with a surrogate endpoint*. This methodology (non-inferiority trial) has been clearly validated in these low-risk patients by two previous studies carried out by the same French thyroid network (TuThyRef) and published in the New England Journal of Medicine, ESTIMABL[40] and ESTIMABL2 [41]. The surrogate endpoint in the present study is the rate of excellent response as defined by the ATA,[13] or complete remission, at 1 year.

If our study confirms the non-inferiority of total thyroidectomy alone, prophylactic central compartment neck dissection could be abandoned for these low-risk patients without taking undue oncologic risks. Secondary endpoints may also show a benefit in terms of patient quality of life and of cost-utility analysis with a total thyroidectomy alone. Patients, physicians, and healthcare providers would all benefit from less-extensive surgery.

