### Objectives

#### Primary objective

To assess the non-inferiority of total thyroidectomy alone as compared to total thyroidectomy with bilateral prophylactic central compartment neck dissection in terms of the rate of complete remission (excellent response) at 1 year after randomization, for differentiated thyroid cancer cT1bT2N0. We hypothesize that the rate of complete remission after thyroidectomy alone is not inferior to the rate of complete remission after thyroidectomy with PND by more than 5% at 1 year.

The primary criterion is the rate of patients *in complete remission* (excellent response) at 1 year after randomization (8+/2 months post-^131^I) as defined by the presence of all 3 criteria:Normal whole body scan (SPECT-CT) performed after the administration of 30 mCi (1.1 GBq) of 131I administered within 2–4 months following surgery,Normal neck ultrasound 8+/−2 months after the ^131^IUnstimulated ultrasensitive thyroglobulin while on L-thyroxine treatment (usTg/LT4) ≤ 0.2 ng/mL) without anti-Tg antibodies (TgAb) 8+/−2 months after administration of ^131^I

In this network’s previous study, 94% of the low-risk patients (including 12% T2N0) were in complete remission 1 year after surgery and administration of 131I after rhTSH [40]. In a similar prospective multicentre trial, 90.2% of the low-risk patients, including patients T1–T3 N0–N1 with or without central compartment neck dissection, were in complete remission 1 year after surgery and administration of 131I after rhTSH [42]. For low-risk patients showing an excellent response after treatment, the risk of recurrence is estimated to be 2–3% [4].

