##### Radioactive iodine

All patients will have Tg/LT4 measured 8 +/− 2 weeks postoperatively, before stimulation with recombinant human thyrotropin (rhTSH).

Then, for all patients (whichever the group), radioactive iodine will be administered after 2 months but within 4 months postoperatively: 30 mCi (1.1 GBq) ^131^I after stimulation with human recombinant thyrotropin (rhTSH)

A ß-HCG test (serum or urine) will be performed before any radioiodine administration.

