### Outcomes: Primary criterion

The primary criterion is the rate of patients *in complete remission (excellent response) at 1 year after radomization* as defined by the presence of the 3 criteria:Normal whole body scan (SPECT-CT) at the time of administration of ^131^I [SPECT-CT will be performed 2–5 days after the administration of 30 mCi (1.1 GBq) of ^131^I after stimulation using injected recombinant human TSH (rhTSH)],Normal neck ultrasound at 8+/−2 months after ^131^I administrationUnstimultaed ultrasensitive thyroglobuline while on L-thyroxine treatment (usTg/LT4) ≤ 0.2 ng/mL without anti-Tg antibodies (TgAb) at 8+/−2 months after ^131^I administration

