## Discussion

The main objective of this study is to show the non-inferiority of total thyroidectomy alone as compared to a total thyroidectomy with a bilateral prophylactic central neck dissection in clinically low-risk patients. This trial will ultimately include a number of patients with intermediate risk factors (Haugen) found on finally pathology. This is the rationale for administering an ablative dose of RAI to all patients, despite the fact that RAI is no longer systematically indicated for pathologically low-risk tumors.(Leboulleux 2022). A secondary objective, however, is to also compare the thyroglobulin levels 8 weeks after surgery and before administration of RAI in each group, to evaluate outcomes without RAI. The need for a total thyroidectomy for low-risk tumors has also been questioned (Haugen); unfortunately, this clinical trial is designed only to answer one question, that is, the utility of PND, and is not suited to answer other questions concerning “downgrading” of surgery for low-risk tumors.

Centers not including patients may be subjected to closing. Centers in France and outside of France may be added as investigators, subjected to approval of an amendment to the study by the national authorities (National Agency for Drug Safety, “Agence Nationale de la Sécurité du Médicament et des Produits de Santé, ANSM) and the French nationa research ethics committee (Comité de Protection des Personnes, CPP). In the event of other amendments, they will also be subjected to the above-cited national authorities for safety and ethical evaluation. The promotor data managing committee will communicate any approved protocol modifications to the participating centers.

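### The abstract concludes without condition that neck dissection is unnecessary, but the confirmatory comparison covers only patients who all receive radioactive iodine before the 1-year ultrasound and thyroglobulin

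*Protocol article*

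**What the plan says.** The abstract's paragraph on potential implications states that a positive trial means "prophylactic neck dissection will have been shown to not be necessary in clinically low-risk papillary thyroid carcinoma". The section Rationale: choice of comparators says that "prophylactic central compartment neck dissection could be abandoned for these low-risk patients without taking undue oncologic risks".

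On treatment, the section Radioactive iodine says that "for all patients (whichever the group), radioactive iodine will be administered after 2 months but within 4 months postoperatively". On timing, Outcomes: Primary criterion says "SPECT-CT will be performed 2–5 days after the administration of 30 mCi", and Primary objective requires "Normal neck ultrasound 8+/−2 months after the" iodine dose, with thyroglobulin (Tg) and anti-Tg antibodies in the same window.

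On earlier studies, Background and rationale says that measuring Tg before and after RAI will "eliminate this bias found in most of these studies in which outcomes were evaluated after RAI ablation in most or all patients". The Discussion explains why every trial patient receives RAI, while noting that "RAI is no longer systematically indicated for pathologically low-risk tumors".

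The oncologic outcome measured before RAI is Tg at 8 ± 2 weeks after surgery. It is secondary, and the statistical methods section assigns it a chi-square comparison.

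**The concern.** A non-inferiority conclusion belongs to the treatment regimen in which the arms were compared. Here RAI is part of that regimen in both arms. The introduction reports, as an argument of those opposed to PND, that RAI treats microscopic nodal disease. If so, RAI acts on the same disease that PND would remove, and the arm difference after RAI may be smaller than the difference without it.

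The Discussion's statement that RAI is not routine for pathologically low-risk tumours makes this matter. The unconditional sentence in the abstract reaches patients who would not receive the background treatment that was tested. A positive result could be cited to omit PND in them, although the primary analysis says nothing about them.

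**Working it through.** **1. Endpoint timing against RAI (RAI is given 2–4 months after surgery, both arms).**

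| Primary component | When read | Can RAI improve it? |
|---|---|---|
| SPECT-CT | 2–5 days after RAI | No; RAI makes the scan possible, and a focus seen counts as failure |
| Neck ultrasound | 8 ± 2 months after RAI | Yes |
| Unstimulated Tg ≤ 0.2 ng/mL, no antibodies | 8 ± 2 months after RAI | Yes |

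All three follow RAI, but only two can be improved by it.

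**2. Where the RAI condition appears.** It is in the abstract's aim and in Background and rationale. It is absent from the abstract's conclusion, from the closing claim in Rationale: choice of comparators, and from the objective as restated in Explanation for the choice of comparators. Primary objective carries it indirectly, because the criterion is timed from the iodine dose.

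**3. The bias claim.** Background and rationale faults earlier studies for judging outcome after RAI in most or all patients. In this trial the primary endpoint is judged after RAI in all patients. The claim of removing that feature fits only the secondary Tg at 8 ± 2 weeks.

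**4. The plan's own figure, for context.** The formula n per arm = (1.960 + 0.842)² × 2p(1 − p)/0.05² gives 298.3, rounded up to 299, at p = 0.95. That matches 598 in total, although the article does not state 95%. The 598 patients and the 5-point margin apply to the post-RAI endpoint only.

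**5. Illustration of attenuation.** Let D be the deficit of thyroidectomy alone without RAI, and f the fraction of it that RAI clears. The documents give no value for f, so it is an assumption shown over a range.

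- Deficit seen after RAI = D(1 − f).
- A 5-point deficit after RAI corresponds to 5/(1 − f) without it: 6.7 points at f = 25%, 10 points at 50%, 25 points at 80%.
- Chance of declaring non-inferiority = Φ[(0.05 − D(1 − f))/SE − 1.96], with SE = √{[p₁(1 − p₁) + p₂(1 − p₂)]/299}, p₁ the rate with PND and p₂ = p₁ − D(1 − f).
- Example: p₁ = 0.94, D = 0.05, f = 0.5 give p₂ = 0.915, SE = 0.0212 and Φ(0.025/0.0212 − 1.96) = Φ(−0.78) = 0.22.

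| p₁ | D | f = 0 | 25% | 50% | 80% |
|---|---|---|---|---|---|
| 94% (cited) | 5 points | 2.5% | 8% | 22% | 51% |
| 90.2% (cited) | 5 points | 2.5% | 7% | 16% | 36% |
| 94% (cited) | 10 points | 0.0% | 0.1% | 2.5% | 30% |

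These are not error rates of the trial's test. Disease that the SPECT-CT shows still counts as failure, so f applies only to what the scan misses. A deficit without RAI is also not strictly defined on the full endpoint, because the scan cannot exist without RAI.

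**6. Can the pre-RAI Tg carry the broad claim?** A non-significant chi-square test does not show non-inferiority, and the article sets no margin for this outcome. At an assumed 80% rate in both arms with 299 per arm, SE = √(2 × 0.80 × 0.20/299) = 0.0327. The 95% interval would be about ±1.96 × 0.0327 = ±6.4 points. Power against a 5-point margin would be Φ(0.05/0.0327 − 1.96) = 33%. It can support the primary result but cannot confirm the broad claim.

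**The case against.** The strongest reply is that nothing is hidden. The abstract's aim names adjuvant RAI, its methods say all patients receive it, the introduction repeats that both groups do, and the Discussion gives the reason: some patients will prove to have intermediate-risk features on final pathology. It also assigns the pre-RAI Tg to the question of outcome without RAI. This stands. A reader might infer that the design is undisclosed or that giving RAI to everyone is a fault; the document supports neither.

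A reader might also infer that RAI masks the whole primary endpoint. It does not: an iodine-avid node seen at 2–5 days fails the patient whatever RAI later achieves.

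Two passages are milder than they first look. The rationale section speaks of "these" patients in "prophylactic central compartment neck dissection could be abandoned for these low-risk patients without taking undue oncologic risks", which can mean the trial's own population. The bias sentence has the before-and-after Tg measurements as its subject. And the view that RAI clears micrometastases is reported as an argument of one side, not as the trial's own expectation.

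None of this puts the missing condition into the abstract's conclusion. Nor does it tell the reader of the bias sentence that the primary endpoint is itself judged after RAI.

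**Conclusion.** The point holds as one of scope. Followed as written, the plan gives a conclusion wider than its confirmatory contrast, and it leaves the pre-RAI outcome to a difference test that cannot show non-inferiority.

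It would go too far to say that RAI inflates the trial's false-positive rate. The hypothesis concerns outcome 8 ± 2 months after RAI, and for that hypothesis the one-sided 0.025 test keeps its level. The 8%, 22% and 51% above describe a different question, outcome without RAI, under an assumed f. They show only that a deficit beyond 5 points without RAI is compatible with a positive trial. The true size cannot be obtained from the document.

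The data, the margin, the decision rule and the treatment are unaffected. What changes is what may be concluded.

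**What to change.** 1. In the abstract's potential implications, limit the conclusion to patients who receive adjuvant RAI after total thyroidectomy, as the abstract's aim already does. For consistency, do the same in Rationale: choice of comparators and Explanation for the choice of comparators.
2. In Background and rationale, limit the bias claim to the pre-RAI Tg outcome, and state that the primary endpoint is assessed after RAI in all patients.
3. In the statistical methods for secondary outcomes, report the between-arm difference in the proportion with unstimulated Tg ≤ 0.2 ng/mL at 8 ± 2 weeks, with a 95% confidence interval. Describe it as supportive evidence on outcome without RAI.

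The cost is wording plus one estimate from data already collected. No patients, visits or tests are added, and no change to treatment is implied. The downside is a narrower headline claim.

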**Trial registration:**

NCT 03570021. June 26,2018

**Supplementary Information:**

The online version contains supplementary material available at 10.1186/s13063-023-07294-0.

## Introduction

### Background and rationale

For most cancers, the extent of metastasis to regional lymph nodes is a prognostic factor, and prophylactic treatment of lymph node basins for patients with no preoperative evidence of nodal disease (cN0) is often recommended. For differentiated thyroid cancer, however, the prognostic role of prophylactic central compartment neck dissection (PND) associated with total thyroidectomy for patients cN0 constitutes a major controversy for these tumors with an increasing incidence, but a very low mortality rate.

Those in favor of PND for whom it is a standard of care cite the low-level evidence suggestingImproved recurrence-free survival (retrospective case series), [1–3]A higher rate of recurrence in the presence of lymph node metastases (in some retrospective studies) and the usefulness of a complete staging in the neck to stratify for radioactive iodine treatment, [4, 5]The technical difficulty of performing a reintervention in the central compartment secondarily, andThe absence of increased permanent complications of PND (in experienced hands). [3]

Opponents of PND cite the low-level evidence suggestingNo effect on oncologic outcomes with PND (retrospective case series), [6, 7]The low rate of recurrence and mortality even without PND, [8]The efficacy of radioactive iodine to treat microscopic nodal metastases,A higher risk of complications (hypoparathyroidism and vocal fold paralysis) as compared to -thyroidectomy alone, [9]The feasibility of reoperation in the central compartment if needed with a relatively low risk of complications (in experienced hands), [10, 11] andAn increase in cost with PND. [12]

Despite the low-level conflicting evidence, different professional societies in several countries have published recommendations for or against the routine use of PND, with consequences for patients, physicians, and healthcare providers [13–19]. The French Society of Otolaryngology Head and Neck Surgery recommends PND [15] whereas the Francophone Association of Endocrine Surgery does not recommend it [19].

This study aims to provide level I evidence with a multicenter prospective open randomized non-inferiority trial comparing bilateral PND with total thyroidectomy to total thyroidectomy alone (and adjuvant radioactive iodine in both groups) for low-risk papillary thyroid cancer patients cT1bT2N0 in terms of the rate of complete remission at 1 year after randomization. We hypothesize that thyroidectomy alone is not inferior to thyroidectomy with PND by more than 5% at 1 year.

Differentiated thyroid carcinoma is the most common endocrine malignancy, with an increasing incidence in part related to an improvement in screening for small tumors by neck ultrasound. It accounts for 80% of all thyroid cancers and ranks as the sixth most common cancer in females in incidence, with approximately 10,000 new cases per year in France [20, 21]. The high disease-specific survival rates favor optimizing treatment and follow-up to minimize complications and overtreatment. Macroscopic lymph node metastases detected on preoperative ultrasound (cN1) are known to increase regional recurrence, with the risk of recurrence related to the size and number of metastatic nodes and the presence or absence of extranodal tumor extension;[22, 23] in this case a therapeutic central compartment neck dissection is currently recommended with no controversy [13].

However, the role of systematic prophylactic neck dissection (PND) in the absence of suspected neck metastases on preoperative ultrasound (cN0) remains controversial. For example, guidelines from the American Thyroid Association (ATA),[13] The European Society of Endocrine Surgeons,[24] the German Association of Endocrine Surgeons,[16] and the Francophone Association of Endocrine Surgery [19] do not recommend PND. The British Thyroid Association [17] and the Japanese Association of Endocrine Surgeons [14] recommend PND in certain cases (large tumors, older patients, and extrathyroidal extension, for example). Finally, the 2012 guidelines from the French Society of Otolaryngology Head and Neck Surgery recommend systematic PND [15].

All of these recommendations are grade C (“expert opinion”) due to the lack of high-level evidence in the field. The proponents of systematic PND have underlined its potential effect on recurrence-free survival and disease-specific survival, shown in some retrospective studies, [1–3] but not found in several meta-analyses [6, 25, 26]. The opponents of systematic PND have emphasized that the prognostic role of occult metastases has not been demonstrated and that radioactive iodine is effective in treating micrometastases [27, 28]. PND may also involve greater morbidity in terms of transient hypoparathyroidism [9]. A higher level of evidence is needed to optimize treatment of these low-risk tumors, which make up the majority of differentiated thyroid cancers.

Current practice is based on conflicting data from studies with low-level evidence and due to the absence of a randomized trial, conflicting recommendations as to the optimal management of low-risk thyroid cancer will prevail [29].

A PubMed® literature search using the terms “thyroid cancer prophylactic neck dissection” found 512 results (accessed January 2023). Among these, Table 1 resumes those with the highest level evidence (meta-analysis of randomized trials, prospective randomized trials, and meta-analyses of retrospective studies). The majority of these studies do not show a difference in locoregional recurrence between total thyroidectomy with PND versus total thyroidectomy alone.

**Table 1 Tab1:** Summary of publications with the highest level of evidence

**Study**	**Design**	**Number of patients**	**Results concerning recurrence rates**	**Other oncologic results**	**Complication rates**
Sanabria A et al Ann Surg 2022 [30]	Meta-analysis of 5 randomized studies	763 409 PND 354 TT	No difference in structural recurrence rate 2.5% vs 2.7%	No difference in biochemical recurrence rate	No difference in rate of permanent hypoPTH
Ahn JH et al Surgery 2022 [31]	Propsective randomized single center	101 51 PND 50 TT	No difference in structural recurrence rates or successful ablation		No difference in complication rate
Sippel R et al Ann Surg 2020 [32]	Propsective randomized single center	60 30 PND 30 TT	No difference in stimulated Tg levels at 6 weeks or 1 year		
Lee DY et al JCEM 2015 [33]	Propsective randomized single center	257 153 PND 104 TT	No difference in LRR 3.3% vs 3.9%	No difference in number of patients treated with RAI	Higher rates of temporary hypoPTH (*p*=0.043)
Viola D et al JCEM 2015 [34]	Propsective randomized single center	181 93 PND 88 TT	No difference in LRR (7.5% vs 8.0%)	More RAI in TT alone group (*p*=0.002)	Higher rate of permanent hypoPTH in PND group (*p*=0.02)
Chen L et al World J Surg 2018 [26]	Meta-analysis of retrospective studies	18,376 11,098 PND 5583 TT	Lower LRR in PND group 2.52% vs 4.59% (OR=0.65)		Higher rates of temporary (OR=2.23)and permanent hypoPTH (OR=2.22)and temporary VFP (OR=2.03)
Liang J et al Acta Otorhino Ital 2017 [35]	Meta-analysis of retrospective studies	6823 3312 PND 3511 TT	Lower LRR in PND group (*p*<0.01)		Higher rate of temporary (*p*<0.01) and permanent (*p*<0.01) hypoPTH and temporary VFP (*p*=0.023) in PND group
Zhao W et al Ann Surg Oncol 2016 [36]	Meta- analysis of retrospective studes	4437 1969 PND 2468 TT	Lower LRR in PND group 1.1% vs 3.4% (*p*=0.002)	More RAI in PND group 74.6% vs 59.9% (OR 1.20)	Higher rates of temporary (*p*<0.00001) and permanent (*p*=0.03) hypoPTH
Wang TS et al Ann Surg Oncol 2013 [6]	Meta- analysis of retrospective studes	1740 745 PND 995 TT	No difference in LRR		No difference in rates of permanent complcations
Lang BH et al Thyroid 2013 [7]	Meta-analysis of retrospective studies	3331 1592 PND 1739 TT	Lower LRR in PND group 4.7% vs 8.6% (OR=0.65)	More RAI in PND group 71.7% vs 53.1% (OR=2.60)	Higher rate of temporary hypoPTH PND group 26% vs 10.8% (OR=2.56)
Zetoune T et al Ann Surg Oncol 2010 [37]	Meta-analysis of retrospective studies	1264 396 PND 868 TT	No difference in LRR (2.02% vs 3.92%)		

Abbreviations: *PND* prophylactic central neck dissection, *TT* total thyroidectomy without prophylactic neck dissection, *LRR* locoregional recurrence rate, *RAI* radioactive iodine, *hypoPTH* hyypoparathyrodism, *Tg* thyroglobulin, *VFP* vocal fold paralysis, *OR* odds ratio

Our study differs from these published studies in the following ways:Our study includes only tumors ≥11 mm (microcarcinomas are not eligible), whereas all of the studies cited in Table 1, with the exception of the study by Sippel et al. [32], included a large proportion of microcarcinomas (in Ahn et al. [31] for example, 90% of the tumors were T1 with a mean tumor size of 1.1 +/− 0.6 cm);Thyroglobulin measurements will be evaluated before and after the administration of RAI to evaluate the effect of RAI ablation and eliminate this bias found in most of these studies in which outcomes were evaluated after RAI ablation in most or all patients;Finally, our study is designed with a non-inferiority margin of 5% and an alpha level set at 0.025, whereas the study by Viola et al. [34] is significant but with a non-inferiority margin of 15% and an alpha of 0.05.

